### **Data reduction**

Data of the 20mSRT will be used to characterize participants' fitness level and to define the intensity of the exercise during iE performance in the second session. Individual maximum velocity ( $V_{max}$ , km/h) will be calculated using the last completed stage ( $E_{max}$ ) (Léger et al., 1988).

$$V_{max} = 0.5 \cdot E_{max} + 8$$

$VO_2max$  will be estimated based on the participant  $V_{max}$  and age ( $y$ , years) (Léger et al., 1988):

$$VO_{2max} = 31.025 + (3.238 \cdot V_{max}) - (3.248 \cdot y) + (0.1536 \cdot y \cdot V_{max})$$

Individual heart rate (HR) will be monitored by a Polar RS800CX (Polar Electro) and it will be synchronized with the time of the 20mSRT test (session 1) and with the iE intervals (session 3). Maximal HR (HRmax) during the childhood and adolescence periods is typically above 200 b/min. Therefore, we will use this value as a reference to assess maximal effort level in the last part of the 20mSRT (Armstrong & Fawcner, 2007). In addition, the mean HR during the iE intervals (85% and 60% of the estimated VO2max) will be calculated (HR-85%VO2max and HR-65%VO2max). These values will be used to further characterize the exercise's intensity during the iE.

The rVMA data fitting and reduction will be done using custom-made MATLAB R2014b programs (The MathWorks, Inc.). Cartesian x-y positions will be low-pass filtered using an eight-order dual-pass Butterworth filter with a cut-off frequency of 12Hz. Accepted trials will have to fulfill the following conditions: startup position found within 20% of the center-to-target distance, and travelled distance equal or higher to 90% of the center-to-target distance. Movement onset of the accepted trials will be defined as the nearest point in an outward movement equal to a 10% of the center-to-target distance. Movement offset will be defined as the first point where speed decreased to a 10% of the max speed value. The adaptation set will be divided in epochs of 8 trials for analysis purposes.

fNIRS and fDCS data, will be converted into changes in concentration levels of oxyhemoglobin ([O2Hb]), deoxyhemoglobin ([HHb]), cerebral metabolic rate of oxygen extraction (CMRO2), and microvascular cerebral blood flow (CBF). A subject-specific differential path-length factor (DPF) will be used for this conversion based on the age of the participant (Duncan et al., 1996; Scholkmann & Wolf, 2013). Data will be low-pass filtered to avoid excessive frequencies that will belong to normal physiology activity and noise from respiration and heart beats or movements (typically a cut-off frequency of 0.1 Hz). Filtered data will be normalized relative to the individual values found in the reference resting state measures. All these processes previous to calculate the variables will be computed using custom made programs.

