### **The rotational visuomotor adaptation task (rVMA)**

During the rVMA participants will be seated in a quiet room, in front of a 19-inch computer screen located at 1m and at eye level. With their dominant hand, participants will be asked to grasp a joystick, maintaining a claw-type grip, an elbow flexion of  $90^\circ$  and a comfortable shoulder position while the forearm rests on a flat surface (Figure 2a). The height and position of the joystick will be adjusted to meet the position criteria. The joystick movement controls a green dot on the screen (1x1cm). Individual targets will randomly appear on screen as red dots (1x1cm) in eight possible locations (45, 90, 135, 180, 225, 270, 315 and  $360^\circ$ ) and at a radius distance of 13 cm from the center. A new target will appear every 2 s and will remain visible for 750 ms. Participants will be instructed to move the green dot, starting from the center of the screen, over the target (red dot) and back to the center as fast and as straight as possible in a single move. During the task a visual-motor mismatch between joystick movement and screen cursor movement is applied by rotating the movement of the cursor, so the greater the rotation the greater the deviation of the cursor according to the movement of the joystick (for example see Ferrer-[name] et al., 2018). Cartesian x-y coordinates of the joystick movement and time will be registered at 120Hz through a NI-6008 card (National Instruments Corporation).

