## Variables

The movement during the rVMA task will be described by the calculated movement time (MT, ms), travel distance (TD, cm) and reaction time (RT, ms) variables. RT will be defined as the time between target appearance and movement onset. Movement output error will be measured through the initial directional error (IDE, deg) and root mean square error (RMSE, cm) variables (Figure 5). IDE will be calculated as the absolute angular difference between the ideal trajectory, a linear vector from the center to the target, and the early real trajectory, defined by the linear vector from the center to the green dot position at the time of 80 ms after movement onset. IDE will be used as a measure of the rotation adaptation or motor consolidation avoiding the possible trajectory correction through perceptual feedback (Contreras-Vidal et al., 2005; Ferrer-[name] et al., 2018, 2017). RMSE will be calculated to represent the straightness of the movement between the ideal trajectory and the real joystick trajectory following the procedure described in Contreras-Vidal et al. (2005):

$$RMSE = \sqrt{\sum_{i=1}^N [(x_1 - x_2)^2 + (y_1 - y_2)^2] \frac{1}{N}}$$

where  $(x_1, y_1)$  and  $(x_2, y_2)$  are the coordinates of the real and ideal trajectory, respectively, and  $N$  is the number of points in the path. Movement straightness (i.e., RMSE) includes the initial deviation from the ideal trajectory (IDE) and the remaining movement trajectory, which could be corrected using perceptual feedback. All these variables will be calculated for each set (baseline, adaptation, RT1h, RT24h, and RT7d). Considering the large inter-subject variability usually presented by children, computed mean adaptation and retention variables will be normalized by subtracting the participant's mean baseline values.

It is proposed that DCD groups will show more variability than their TD peers (King, Haring, Oliveira, & Clark, 2011; Roche et al., 2016; Smits-Engelsman & Wilson, 2013). Inter-trial variability will be calculated via SD for all performance variables in the rVMA (MT, MT-SD, TD, TD-SDRT, RT-SD, IDE, IDE-SD, RMSE, and RMSE-SD) to characterize the groups.

During the adaptation set, data typically present an initial rapid-error decay followed by a slower decline. As it has been seen in other studies (Ferrer-[name] et al., 2018, 2017; Krakauer, Ghez, & Ghilardi, 2005), these data from adaptations seem to be best fitted by a double exponential function:

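### The rVMA trial-acceptance rule is purely spatial, so anticipatory trials, even with a reaction time of zero or less, can be accepted and can distort IDE, IDE-SD and RT-SD

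*Protocol*

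**What the plan says.** The Data reduction section sets the rule: "Accepted trials will have to fulfill the following conditions: startup position found within 20% of the center-to-target distance". Its second condition is a travelled distance of at least 90% of that same length. Both conditions are distances. The same section sets movement onset, "defined as the nearest point in an outward movement equal to a 10% of the center-to-target distance". The Variables section adds "RT will be defined as the time between target appearance and movement onset", with no minimum or maximum, and reads IDE from the cursor position 80 ms after onset.

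The rVMA section gives the pacing, "A new target will appear every 2 s and will remain visible for 750 ms", and the layout: "Individual targets will randomly appear on screen as red dots (1x1cm) in eight possible locations", "at a radius distance of 13 cm from the center". It describes no variable interval and no catch trials.

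On variability, the Variables section says "Inter-trial variability will be calculated via SD for all performance variables in the rVMA". H1 predicts that children with DCD will be more variable than TD children.

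**The concern.** When the target appears is predictable; where it appears is not. A child who starts in rhythm, before seeing or using the target, is guessing the direction. IDE is sampled early precisely so that feedback cannot correct it, so a guess enters the error measure at full size. It is then scored as poor adaptation and high variability, although it reflects timing or impulsivity rather than the visuomotor map.

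Three outcomes are exposed: IDE (the adaptation and consolidation measure, and the basis of the sample size), IDE-SD and RT-SD. Guess rates could plausibly differ by cohort. ADHD is admitted in the DCD cohort, while TD children must have no problem affecting motor learning.

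**Working it through.** The protocol states no figure on this point, so there is none to reproduce. The check has five steps.

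**1. Geometry (from the protocol).** The distance is 13 cm. Onset is 0.10 × 13 = 1.3 cm, the start tolerance 0.20 × 13 = 2.6 cm, and the travel minimum 0.90 × 13 = 11.7 cm. I read the startup position as the cursor position when the target appears. A cursor between 1.3 and 2.6 cm out at that moment has already passed onset (RT ≤ 0) and still meets the start condition. The travel condition tests length, not direction.

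**2. How early a launch can pass (assumed minimum-jerk stroke of duration T).** The path fraction 10x³ − 15x⁴ + 6x⁵ reaches 10% at 0.247T and 20% at 0.327T.

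| T (assumed) | 10% reached | 20% reached |
|---|---|---|
| 300 ms | 74 ms | 98 ms |
| 500 ms | 123 ms | 163 ms |
| 600 ms | 148 ms | 196 ms |
| 750 ms | 185 ms | 245 ms |

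With T = 500 ms, launches up to 163 ms before the target pass, and those 123 to 163 ms before it have RT ≤ 0.

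**3. Error of a guess.** Over eight directions the absolute error averages (0+45+45+90+90+135+135+180)/8 = 90 degrees, SD 55. With a full 60-degree offset it is (60+105+150+165+120+75+30+15)/8 = 90 degrees.

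**4. Effect on the SD.** With guess rate p, valid mean m and SD s: SD = √[(1−p)s² + p·55.1² + p(1−p)(90−m)²]. Take m = 20 (assumed).

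| p | s = 15 | s = 20 | Difference |
|---|---|---|---|
| 0 | 15.0 | 20.0 | 5.0 |
| 2% | 19.4 | 23.4 | 4.0 |
| 5% | 24.5 | 27.7 | 3.2 |
| 10% | 30.8 | 33.2 | 2.5 |

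- Equal true SD of 15 with guesses at 5% v 2% gives a false difference of 24.5 − 19.4 ≈ 5.0 degrees.
- A true 20 v 15 with guesses at 2% in DCD and 5% in TD reverses sign: 23.4 − 24.5 ≈ −1.0 degrees.
- For RT (valid trials 350 ms, SD 80; guesses 0–150 ms; all assumed), 5% guesses move the mean to 336 ms and RT-SD to 99 ms.

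**5. Simulated test of IDE-SD.** 30 v 30 children, 104 trials, t-test, 1,000 runs. The last column assumes that every guess is removed. Valid absolute errors come from a normal with mean 15 and the spread shown; guess rates vary between children.

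| Spread DCD v TD | Guesses DCD v TD | Rejects, rule as written | Rejects, all guesses removed |
|---|---|---|---|
| 15 v 15 | 5% v 2% | 89% | 4.9% |
| 15 v 15 | 5% v 5% | 5.4% | 4.0% |
| 20 v 15 | 5% v 5% | 12% | 97% |

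With spread 20 v 15 and guesses 2% v 5%, the mean difference is −3.2 degrees as written and +2.8 with guesses removed.

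A second model (motor noise SD 10 degrees, several between-child spreads of guess rate) gives, as written against all guesses removed:

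- Equal noise, 5% v 2% guesses: 85–98% false positives against 4–8%.
- True noise 12 v 10, 5% guesses in both groups: power 4–5% against 88–90%; with 2% in both, 5–9% against 87–90%.
- Equal noise, smaller gaps, as written only: 20–42% false positives at 3% v 2%, and 13–25% at 1.5% v 1%.

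The results depend on the model. For the 20 v 15, 5% case, the formula in step 4 with a fixed between-child SD of 5 degrees gives power 0.70, not 12%. In the simulation, taking absolute values shrinks the true SD gap to about 2.7 degrees, and varying guess rates widen the spread between children.

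**The case against.** The strongest reply is that the size is all assumption. No guess rate, motor noise, stroke time or between-child spread is in the protocol; the launch window falls to 98 ms for a 300-ms stroke; and equal guess rates create no false difference. That stands. A reader might infer that any DCD-TD variability difference in this trial would be an artefact, or that the H1 test is already known to be biased. The documents support neither. They show that the rule admits such trials, not how many there will be.

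A reader might also infer that a simple 150-ms floor on RT restores nominal error and full power. It does not. RT runs to the 10% point, reached 148 ms after launch for a 600-ms stroke, so the floor removes only launches up to about +2 ms. If guesses launch evenly from 196 ms before to 150 ms after the target, 148/346 ≈ 43% survive. With that leak in the second model, false positives at 5% v 2% remain 49–87%, and power for 12 v 10 with 5% guesses in both groups stays at 5–8%.

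The claim that exercise would distort the retention result through arousal is also weak. H1 predicts an exercise benefit for consolidation, retention is tested at 1 h, 24 h and 7 days, and nothing in the protocol suggests that anticipation is raised that late. Mean IDE is baseline-subtracted, and a stable rate p largely cancels: [m₁ + p(90−m₁)] − [m₀ + p(90−m₀)] = (1−p)(m₁−m₀), a 5% shrinkage at p = 5%. The SDs have no such protection.

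Dropping these trials from RT and RT-SD is partly a choice of what to measure, since the Attention section treats RT as a marker of sustained attention and the DCD cohort deliberately admits ADHD. That stands too, and limits the remedy.

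Finally, reaction-time trimming is often left to a SAP, the list is not said to be exhaustive, the SDs are introduced to characterise the groups, and the sample size rests on IDE rather than IDE-SD. This lowers the weight but does not remove the point: the protocol itself fixes the acceptance conditions, and its onset and start thresholds together admit RT ≤ 0.

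**Conclusion.** The point holds as a flaw in a stated rule. Trials begun before the target could be used can be accepted, and they inflate IDE, IDE-SD and RT-SD. Unequal guess rates can create a group difference in variability; equal rates of a few percent can mask a true one. Under the assumptions shown, 5% v 2% guesses produce a false IDE-SD difference in roughly 85–98% of simulated trials, while 1.5% v 1% produces one in 13–25%. Every such figure is conditional on inputs the documents do not give, and those with guesses removed assume perfect removal. The change is worth making before group data are seen. The point does not show that the trial's conclusions would be wrong.

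**What to change.** Add a third acceptance condition to Data reduction, applied to IDE, RMSE and their SDs, that excludes anticipatory trials. Fix it before group data are seen and match it to the 10%-distance onset, in one of two ways:

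- Detect launch by tracking back from the 10% point on the speed trace, and apply the minimum latency to launch.
- Set the RT floor from pooled, group-blind baseline (0-degree) trials, as the shortest RT at which initial direction is better than chance.

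Report the anticipation rate by group and set. Show RT and RT-SD with and without the excluded trials. Give a sensitivity analysis over several floors.

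The cost is a short addition to the rule, a little more analysis, and a few percent of trials if guesses are that common. RT is already computed.

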## Attention

### *Attention as a potential mechanism to explain deficits in motor learning in DCD*

Attention is critical for skill acquisition, with mild or moderate impairments impacting learning efficacy (Boyd, Vidoni, Siengsukon, & Wessel, 2009). Three to four different types of attention have been defined in the literature: orienting, selective, divided and sustained (Fortenbaugh, DeGutis, & Esterman, 2017; Posner, 1990; Raz, 2004). Sustained attention is particularly important when learning has to occur in an invariant, relatively predictable context as in the learning of the rVMA task. A child does not need to divide, select or differently orient its attention when confronted with a computer screen and joystick to control a marker going to predetermined target positions, whether congruently or in a rotated fashion. On the contrary, sustain attention is critical since learning this task requires many practice trials which follow relatively fast. A small break in the maintenance of attention to the task will have large error consequences. In addition, limited capacity to sustain attention may hinder the formation of an internal model necessary to consolidate the task. Important attention related information can be obtained by examining multiples measures of behavior such as the reaction time which has been shown to be highly sensitive to changes in sustained attention (Derosière, Dalhoumi, Perrey, Dray, & Ward, 2014; Fortenbaugh et al., 2017).

A particularly sensitive period of development for sustained attention capacity seems to be between 6 to 9 years of age. Betts, Mckay, Maruff, and Anderson (2006) investigated sustained attention in children with TD between 5 and 12 years of age. They diagnosed a rapid development from 5-6 years to 8-9 years and a developmental plateau from 8-9 years to 11-12 years. Whether this developmental trajectory is the same for children with DCD is not known, but it places a target age range to examine issues of attentional development in children with DCD.

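### Off-centre starts are accepted up to 2.6 cm, but initial directional error is scored from screen centre, which distorts IDE and IDE-SD in the DCD–TD contrasts; the onset rule also lacks a reference point

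*Protocol*

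**What the plan says.** All of the following is in the Protocol.

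- **Task** (The rotational visuomotor adaptation task). Targets lie "at a radius distance of 13 cm from the center". "Participants will be instructed to move the green dot, starting from the center of the screen", and pacing is fixed: "A new target will appear every 2 s and will remain visible for 750 ms". Centring rests on instruction; no enforced re-centring is described.
- **Acceptance** (Data reduction). A trial needs a "startup position found within 20% of the center-to-target distance" and a travelled distance of at least 90% of the same distance.
- **Onset** (Data reduction). "Movement onset of the accepted trials will be defined as the nearest point in an outward movement equal to a 10% of the center-to-target distance". Neither the screen centre nor the actual start is named as the reference.
- **Reaction time** (Variables). "RT will be defined as the time between target appearance and movement onset".
- **IDE** (Variables). IDE is the absolute angle between the centre-to-target line and the early real trajectory, the latter "defined by the linear vector from the center to the green dot position at the time of 80 ms after movement onset". It is the stated measure of adaptation and consolidation. Adaptation and retention means are normalised by subtracting the child's own baseline mean.

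The introduction on attention also gives weight to the "reaction time which has been shown to be highly sensitive to changes in sustained attention".

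**The concern.** The acceptance rule admits movements that begin away from the centre, and the IDE rule then scores direction as if every movement began there. Part of the start offset is read as aiming error. Because IDE is unsigned, these errors do not average out when true error is near zero.

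Returning to the centre within a 2 s cycle is itself a motor skill. The Protocol describes children with DCD as slower, less accurate and more variable (Motor Learning and DCD), so worse centring in that cohort is plausible. If it occurs, mean IDE and IDE-SD will differ between cohorts for a reason unrelated to visuomotor learning. H1 predicts both greater variability and poorer consolidation in DCD, and both are read from these variables.

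The onset rule is a separate matter. Under one of its two readings, reaction time cannot be derived for some accepted trials.

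**Working it through.** **1. Thresholds.** Start window 0.20 × 13 = 2.6 cm. Onset 0.10 × 13 = 1.3 cm. Minimum travel 0.90 × 13 = 11.7 cm.

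**2. Reaction time under the two readings of onset.**

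- *Displacement from the actual start.* Every accepted trial travels at least 11.7 cm, so a 1.3 cm displacement always exists and RT is derivable.
- *Radius from centre.* A start at 1.3–2.6 cm is already past onset when the target appears, so RT is negative, missing, or inflated by a drift back through the centre. This ring is 1 − (1.3/2.6)² = 75% of the accepted disc by area, but area is not a share of trials. With assumed Gaussian start scatter of 0.4, 0.7 and 1.0 cm per axis, the share of accepted trials in the ring is 0.5%, 18% and 41%.

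**3. IDE for perfect aim, under either reading.** Put the centre at (0, 0), the target at (13, 0) and the start at (0, s), perpendicular to the target line. After t cm travelled straight towards the target, with L = √(13² + s²), the cursor is at x = 13t/L, y = s − st/L, and the scored IDE is arctan(y/x). The true aiming error is zero.

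Example: s = 1.3, t = 3.9. L = 13.065, x = 3.881, y = 0.912, so IDE = 13.2°.

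| Offset s (cm) | t = 2.6 cm | t = 3.9 cm | t = 6.5 cm |
|---|---|---|---|
| 0.65 | 11.3° | 6.7° | 2.9° |
| 1.3 | 21.9° | 13.2° | 5.8° |
| 2.6 | 39.3° | 25.6° | 11.7° |

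An offset along the target line gives about 0°.

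**4. Size between two cohorts with identical aiming.** The Protocol gives neither start scatter nor early speed, so these inputs are assumptions: Gaussian starts truncated at 2.6 cm, with scatter 0.4 cm (better centred) versus 1.0 cm (worse centred) per axis; early speed v = 15 or 30 cm/s; aiming noise SD 10° or 15° in both cohorts; onset read as displacement. Travel at scoring is 1.3 + 0.08v = 2.5 or 3.7 cm. Simulation with 400,000 starts per setting:

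| Noise, speed | Baseline mean IDE, 0.4 vs 1.0 cm | Gap | Baseline SD, 0.4 vs 1.0 cm | Ratio |
|---|---|---|---|---|
| 10°, 15 cm/s | 10.0° vs 17.7° | 7.7° | 7.6° vs 14.6° | 1.9 |
| 10°, 30 cm/s | 8.8° vs 12.0° | 3.3° | 6.7° vs 9.4° | 1.4 |
| 15°, 15 cm/s | 13.5° vs 20.0° | 6.6° | 10.2° vs 16.3° | 1.6 |
| 15°, 30 cm/s | 12.5° vs 15.1° | 2.6° | 9.5° vs 11.7° | 1.2 |

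At 0.2 cm scatter with the same noise, mean baseline IDE rises by only 0.1–0.6° over perfect centring.

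**5. Effect of baseline subtraction.** The artefact is largest near zero error and shrinks as true error grows. With starts spread uniformly over the accepted disc and a true error of 60°, mean IDE stays at about 60°. Baseline therefore carries more artefact than a set with residual error, and subtraction over-corrects. Normalised IDE, worse-centred minus better-centred cohort, with identical true error:

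| Noise, speed | True residual 20° | True residual 30° |
|---|---|---|
| 10°, 15 cm/s | −3.4° | −5.2° |
| 10°, 30 cm/s | −2.0° | −2.6° |
| 15°, 15 cm/s | −2.1° | −3.7° |
| 15°, 30 cm/s | −1.1° | −1.7° |

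Negative means that the worse-centred cohort appears to perform better. If a set's true error equals that at baseline, the spurious gap is zero.

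**The case against.** Several stronger claims are tempting, and the Protocol does not support them.

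- *Reaction time is invalid for off-centre starts.* A reader might infer this from 10% being smaller than 20%. The wording speaks of an outward movement of a given size, which fits displacement from the start at least as well as a radius. On that reading RT is sound, so what stands is an ambiguity.
- *A DCD–TD gap of 5–10° and a 2.5-fold SD from centring alone.* These come from the same model with perfect aim. Ordinary aiming noise reduces both, as step 4 shows.
- *Centring error makes DCD retention look worse.* This overlooks the baseline subtraction. For normalised means the artefact runs the other way.
- *Every IDE contrast is biased.* Exercise and rest are randomised within each cohort, and baseline precedes the exercise. No mechanism for bias in that comparison is shown.

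Two further objections carry weight. The scatter and speed values are assumed. The device is a joystick, and whether it self-centres is not stated, so real scatter could be 0.2 cm or less and the effect negligible. A start-referenced IDE also presumes that the child aims from the displaced cursor. A child repeating a learned centre-out direction from a 2.6 cm perpendicular offset would score up to arctan(2.6/13) = 11.3° on it.

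Neither removes the core point: the written rules accept off-centre starts and give a correctly aimed movement from such a start a non-zero error.

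**Conclusion.** The point holds for IDE under both readings of onset, and for RT only as an unresolved ambiguity.

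The exposed analyses are the DCD–TD comparisons of IDE (O1.2 and the Group effects) and IDE-SD. Under the stated assumptions the distortion is about 2.6–7.7° in raw baseline IDE and a factor of about 1.2–1.9 in SD. After normalisation it is about 1–5° in favour of the worse-centred cohort at 20–30° residual error. It can thus inflate H1's variability prediction while masking its consolidation prediction. If scatter is 0.2 cm or less with 10–15° aiming noise, the effect on mean IDE is under 1°.

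The definitional fault is certain. Its size is not, because it depends on start positions that the Protocol does not describe, and on the two cohorts centring differently.

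**What to change.** Before data reduction, amend Data reduction and Variables as follows.

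1. Define onset as 1.3 cm of outward displacement from the recorded cursor position at target appearance.
2. Compute IDE as the angle between the start-to-target line and the vector from the start to the cursor 80 ms after onset. A perfectly aimed movement then scores 0° from any accepted start.
3. Set RT to missing for trials already moving at target appearance, with the criterion for moving fixed in advance.
4. Report the centre-based IDE alongside, for comparability with the earlier studies whose IDE data underlie the sample size.

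The 20% acceptance window can stay. Cursor coordinates are already recorded at 120 Hz, so the change is a few lines in the custom reduction program and needs no new data. The costs are some lost RT values, slightly less comparability with earlier work, and the score of up to about 11° for a child who repeats a centre-out direction from the edge of the window.
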